#### Study 2: retrospective cohort study

Since study 2 is exploratory in nature, no CD outcomes have yet been identified. The following steps will be taken for selection and operationalization of CD outcome variables, CD quality indicators, and CD risk factors:

A structured search for existing quality indicators, outcome variables, and risk factors of orthopedic rehabilitation will be conducted in (a) literature (e.g., Medline, Cochrane Library), (b) medical guidelines (Guidelines International Network), (c) indicator databases (e.g., [42, 43], and (d) documentation of existing procedures of quality assurance in the field of orthopedic rehabilitation. Search results will be assessed for their compatibility with claims data.The nationwide project claims database of AOK-insured patients will be analyzed to identify additional complex healthcare and rehabilitation outcomes for patients that have undergone primary knee or hip arthroplasty. This includes analysis of demographics, medical and other relevant data such as comorbidities, nursing care level, medication use, and utilization of therapeutic health service. The database will encompass data from the individual observational period for each patient, which includes the 24 months pre-surgery as well as 12 months of care after orthopedic rehabilitation. Pre-surgery data will be used as a baseline measure of study population characteristics, while the follow-up period after rehabilitation can be used to identify individual changes in relation to the baseline.Results from step (1) and (2) will be consolidated and CD outcomes and risk factors operationalized. Potential CD outcomes that represent aspects of rehabilitation treatment quality within claims data could be, for example, mobility (through provision of mobility aids), pain medication, or progression to higher nursing care levels. CD outcomes will consider care and quality aspects from all medical sectors. All quality indicators will be defined by denominators and numerators, and descriptions of inclusion, exclusion and exception criteria [44]. Denominators display a specified target population (e.g., all patients undergoing arthroplasty), whereas numerators display the number of people in the target population experiencing a specified outcome (e.g., surgical complications; [44]). These descriptive definitions can later be used to calculate individual values for rehabilitation facilities. Indicators will be translated into coded data (e.g., coded diagnoses, procedures, and prescriptions), and an appropriate reference value will be defined for each indicator.Each CD quality indicator will be adjusted for risk factors that have statistical influence on the indicator rate but cannot be influenced by IRFs. Risk factors might include patient characteristics (e.g., age, sex, comorbidity, nursing care level), or aspects of acute hospital care before rehabilitation. Relevant risk factors will be selected based on current research, results from SHI data analyses, and expert opinion [45].

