
### Data analysis and hypothesis testing

#### Study 1: prospective longitudinal study

Missing values analysis will be performed for each variable. If the results support the assumption of values missing at random or completely at random, they will be imputed via multiple imputation. Within the framework of sensitivity analysis, the hypotheses will be tested with both the raw dataset and the imputed dataset.

##### Hypothesis 1

To test hypothesis H1, the PD outcome variable dataset collected in study 1 will be matched to the CD outcome variable dataset using participants’ national health insurance numbers, which are pseudonymized by a data trustee in accordance with German data protection laws. Three dimensions of diagnostic validation will be evaluated to assess whether the CD variables can serve as proxies for the PD variables (see section “Study outcomes”): accuracy, reproducibility, and precision [46].

Accuracy will be assessed by linear regression, with each PD outcome variable as a dependent and each CD outcome variable as an independent variable. 95% confidence intervals (CIs) will be calculated for the identified intercepts and regression coefficients using the Gaussian approach (95%-CI of a: a ± 2*Se_a_; 95%-CI of b: b ± 2*SE_b_). If the CIs include 0 and 1 (for intercepts and regression coefficients, respectively), accuracy will be considered adequate for the outcome variable.

Reproducibility will be assessed by duplicate standard deviation (SD), which is calculated using the following formula (with *d* as the individual difference between the CD outcome variable and approximated PD outcome variable for each patient):$$\varvec{D}\varvec{u}\varvec{p}\varvec{l}\varvec{i}\varvec{c}\varvec{a}\varvec{t}\varvec{e} \varvec{S}\varvec{D}=\sqrt{1/2\left(\frac{\sum {\varvec{d}}^{2}}{\varvec{n}}\right)}$$

Following the recommendation by Cleophas & Zwinderman [46], reproducibility is considered adequate for a duplicate SD of 10–20%.

Precision will be assessed by comparing the standard deviations of CD outcome variable and approximated PD outcome variable. If the standard deviation of a CD outcome variable is equal or smaller to the standard deviation of an approximated PD outcome variable, precision is considered good or better.

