If at least two of the three validation criteria are met, the tested CD outcome variable is considered an adequate proxy for the respective PD outcome variable. Bland-Altman plots will be used for graphic evaluation of measurement differences [47, 48]. This same procedure will be applied to test H1b using CD quality indicators and PD quality indicators, which are represented by facility group mean values of PD outcome variables.

##### Hypothesis 2

H2 postulates an improvement in risk-adjustment models when considering cross-sectoral claims data, i.e., an increase in (adjusted) R^2^, and will be analyzed with nested multilevel regression models. A basic model (M0) will be estimated for each PD outcome variable using the PD confounders (see Table 2) on level 1. Models will be estimated for each time point after baseline (t1, t2, t3), and will be adjusted for *time* (rehabilitation effect) as a predictor on level 2. Furthermore, level 2 PD quality indicators will be included. Each model will be expanded with previously identified CD risk factors (on level 1 and level 2) as described in section “Study outcomes”. The nested models will be compared with Likelihood Ratio tests [49]. The analysis sample will be randomly divided into two parts, with one half allocated for analysis of risk-adjustment, and the remaining half used to validate the resulting models.

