## Discussion

Health claims data has the potential to simplify current quality assessments in rehabilitation. SEQUAR will evaluate its benefit to quality assurance in orthopedic inpatient rehabilitation: We will explore outcome variables and quality indicators based on readily available statutory health insurance (SHI) claims data, and assess their ability to replace select parts of the current best-practice quality assurance protocol based on arduous primary data collection. If we fail to identify suitable claims data quality indicators, we can demonstrate that the current protocol of assessing patient-reported and physician-reported outcomes via questionnaires is still to be considered the best-practice approach. In the process, we are hoping to improve risk-adjustment models used to evaluate inpatient rehabilitation facility (IRF) quality by incorporating cross-sectoral SHI quality data (i.e., quality of the operating hospital) that could help adjust for risks outside of an IRF’s control.

Many previous studies have explored the utility of claims data in quality of care research. Some have even taken a cross-sectoral approach, like Stegbauer et al. [51] or Bramesfeld et al. [52], though the latter had to cut their trial phase short because–fittingly–the burden of primary data collection for participating physicians proved to be too great. However, to our knowledge, no study has examined claims data’s cross-sectoral potential for quality assurance in inpatient rehabilitation (where quality assessment is particularly difficult due to the variety in outcomes), nor has any research explored the possibility of replacing patient- and physician-reported outcomes with outcomes based on claims data.

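### H1 regresses every questionnaire outcome on every claims outcome and accepts each passing pair; with ten facilities and scaling left undefined, unrelated facility-level pairs can be labelled adequate proxies

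*Protocol article*

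**What the plan says.** The test of H1 stands in the Protocol article under Data analysis and hypothesis testing, Study 1, Hypothesis 1. Accuracy is assessed by regression "with each PD outcome variable as a dependent and each CD outcome variable as an independent variable", and "If the CIs include 0 and 1 (for intercepts and regression coefficients, respectively), accuracy will be considered adequate". The second criterion is the duplicate SD: "reproducibility is considered adequate for a duplicate SD of 10–20" per cent. The third, precision, is met when the SD of the claims (CD) variable does not exceed that of the approximated primary-data (PD) variable.

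The decision rule follows: "If at least two of the three validation criteria are met, the tested CD outcome variable is considered an adequate proxy for the respective PD" measure. For facilities, "This same procedure will be applied to test H1b using CD quality indicators and PD quality indicators", the latter being facility means.

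Three other places bear on this:
- Study outcomes, Study 2: "Since study 2 is exploratory in nature, no CD outcomes have yet been identified". It then sets out a literature search, database analysis and operationalisation to find them.
- Study design and methods: the matched data are split into analysis and validation parts, and a correlation above 0.30 is assumed for H1b. The only detailed use of a split is under Hypothesis 2, for the risk-adjustment models.
- Hypothesis 2 names t1, t2 and t3. Hypothesis 1 names no time point.

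**The concern.** Read as written, the rule gives a separate verdict to every PD-by-CD combination, and any pass turns that CD variable into a proxy. Table 2 has 7 PD outcomes and 15 outcome-by-time values after baseline. The number of CD variables is open. Nothing ties a CD variable to a PD domain by content before the linked data are seen, and nothing says which pairs or how many decide H1a or H1b.

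The accuracy criterion is also passed more easily when its interval is wide, as it is with ten facilities, and the precision criterion ignores association altogether. Chance passes are therefore most plausible for H1b.

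Under Practical implications, the indicators found feed a new quality assurance protocol and facility report cards. The Discussion also draws a conclusion from failure: "If we fail to identify suitable claims data quality indicators, we can demonstrate that the current protocol" remains best practice. Without named deciding pairs, one table of results could be read in support of either conclusion.

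**Working it through.** **Inputs from the article.** Ten facilities. 600 patients with 20% dropout per time point: 600 × 0.8³ = 307, which agrees with the stated n = 300, or about 150 per half. Table 2: 4 patient-reported outcomes × 3 later time points + 3 staff-measured outcomes × 1 = 15 values from 7 outcomes. The article states no error rate for H1, so there is none to reproduce.

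**Assumptions.** Five CD indicators, for illustration. Both facility indicators standardised. PD set and CD set unrelated to each other, with correlation 0, 0.5 or 0.8 within each set.

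**Pass rate per pair, H1b, standardised.**
- The SDs are equal, so precision is met. The intercept is 0, so its interval includes 0. Only the slope is left. Duplicate SD has no percentage base when the mean is zero and is not counted.
- Slope = r, with SE = √((1 − r²)/8).
- Pass if r + 2·SE ≥ 1, that is (1 − r)² ≤ 4(1 − r²)/8. This gives 1 − r ≤ (1 + r)/2, hence r ≥ 1/3.
- At r = 1/3, t = (1/3)·√(8/(8/9)) = 1.0 on 8 df, one-sided p = 0.173.

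**Across pairs (simulated family rates).**

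| Pairs | Expected false passes | At least one, at correlation 0 / 0.5 / 0.8 |
|---|---|---|
| 7 × 1 | 7 × 0.173 = 1.2 | 74% / 52% / 36% |
| 7 × 5 | 35 × 0.173 = 6.1 | >99% / 86% / 58% |
| 15 × 5 | 75 × 0.173 = 13.0 | 100% / 93% / 65% |
| 7 fixed pairs | 7 × 0.173 = 1.2 | 74% / 62% / 45% |

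**Sensitivity to scaling, unrelated pairs, 2-of-3 rule, ten facilities.**
- Common scale with equal means and SDs: 52% pass at a coefficient of variation (CV) of 10%, 33% at 20%, 20% at 30%, 18% at 50%.
- CD SD half the PD SD: 63–98%. CD SD 1.5 times the PD SD: 3–13%.
- Raw, unlike scales (illustration: PD mean 35, facility-mean SD 4; binary CD at 30%): 0.3%.
- The separate threshold r > 0.30: 20%.

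**Patient level, n = 150 or 300.** On a common scale the accuracy criterion is never met by chance. Pass rates are 0–0.3% at CV of 30% or more, but about 25–50% at CV 10–20% with equal SDs. If CD is calibrated to PD by regression, 100% of unrelated pairs pass in the same sample and 84% in an independent one. The raw-scale illustration gives 0%.

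**Would Holm on the stated criterion help?** With multiplier k the threshold is r ≥ (1 − k²/8)/(1 + k²/8). For seven pairs the strictest step has k = 2.69 and k²/8 = 0.90, so r ≥ 0.05. The unrelated pass rate rises from 17% to 45%. Adjustment makes passing easier.

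**A test that does control error.** One-sided test of correlation above 0, first Holm step 0.05/7: t = 3.117 on 8 df, r = 3.117/√(3.117² + 8) = 0.74.

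**The case against.** Much of what is absent (a pair list, a deciding time point, multiplicity control) is what an article leaves to a fuller protocol or analysis plan that is not shown. No list could be printed while CD outcomes were unidentified. The decision rule speaks of the respective PD variable, and Research aims sets pain medication beside patient-rated pain, so matched pairs may be intended. The split in Study design and methods is made on the dataset used for all hypotheses. Nothing in the article standardises the indicators: CD indicators are proportions and PD indicators are scale means.

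The scaling argument stands. A reader might infer that all-pairs screening is bound to yield false proxies at both levels. The article does not support that: on raw, unlike scales almost nothing passes. The raised patient-level rates, at low CV or after calibration, come from the 2-of-3 rule itself and not from the number of pairs.

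The rest removes less. The article is not silent on H1: it prints an each-by-each regression and a numerical acceptance rule. The wording and the example hint at matching but designate no pair. The split is never made a condition for H1, and for H1b both halves would come from the same ten facilities.

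**Conclusion.** The point holds in a limited form. As stated, the H1 procedure can label unrelated facility-level pairs as adequate proxies, and it fixes neither pairs nor a time point against which H1a and H1b are judged. If both indicators are standardised, the chance is 17% per unrelated pair, with about 6 false passes among 35 pairs. The number of CD indicators, the standardisation and the within-set correlations are assumptions. Other scalings move the per-pair rate from under 1% to well above 17%. For H1a, chance passes are near zero unless CVs are low or CD is calibrated to PD.

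Fixing the pairs cuts expected false passes from about 6 to about 1.2. It does not settle H1b, because seven fixed pairs still leave about a 62% chance (45–74%) of at least one.

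**What to change.** Before PD and CD data are linked:
1. Use the selection steps already planned under Study outcomes, Study 2 to fix one content-matched CD variable per PD domain and one deciding time point (for example t3 for patient-reported outcomes and t1 for staff-measured ones, which have no later value).
2. State that H1a and H1b are judged on these pairs only. Report all other pairs as exploratory, without the label of adequate proxy.
3. State the scale on which the three criteria are computed.
4. For H1a, also require a pass in the validation half.
5. For H1b, add a one-sided test of correlation above 0 with Holm control across the fixed pairs. Do not apply Holm to the criterion that the intervals include 0 and 1.

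The cost is analysis-plan wording and a dated list of pairs; no new data are needed. Unexpected pairs become hypothesis-generating only. With ten facilities the H1b test is strict, at about r ≥ 0.74 at the first step for seven pairs, so H1b may have to be reported as descriptive.

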### Study population and recruitment

#### Study 1: prospective longitudinal study

For study 1, ten German inpatient rehabilitation facilities (IRFs) were enlisted in the study by local representatives of the regional AOK health insurance funds, which in turn are recruiting a planned sample of 600 patients. Participating IRFs signed a collaboration agreement with the principal investigator, and each appointed a local study coordinator in charge of organization and implementation of all project tasks (e.g., recruitment of participants, distribution of patient information and consent forms, storing/safekeeping signed consent forms). Patient recruitment began in November of 2022 and will end in December 2023.

Patients eligible for participation are recruited on-site in the beginning of their orthopedic follow-up rehabilitation. Study coordinators present them with a physical copy of the study fact sheet (covering study synopsis, data protection, and other legal aspects), and ask for their participation. Those agreeing to participate sign an informed consent form. Eligibility is determined by meeting the inclusion criteria: Participants must be at least 18 years old at time of inclusion (beginning of rehabilitation), insured through AOK health insurance fund (for purposes of data availability), and receive inpatient orthopedic follow-up rehabilitation after implantation of a knee joint replacement or hip joint replacement due to osteoarthritis. Participants need to demonstrate sufficient knowledge of the German language and sufficient cognitive abilities to answer the comprehensive questionnaires independently. Patients that prematurely discontinue rehabilitation, demonstrate insufficient German or cognitive skills, or change health insurance within the study period will be excluded.

Participation in the study is incentivized with a €50 gift voucher for patients that complete all four questionnaires, while IRFs receive €120 per patient for full patient participation and completed case report forms.

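### For H1b, the ± 2 SE intervals labelled 95% cover about 92% per coefficient, because the facility-level regressions rest on ten points

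*Protocol article*

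**What the plan says.** Under Data analysis and hypothesis testing, Study 1, Hypothesis 1, the Protocol article sets the accuracy criterion in three steps.

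- The model: "Accuracy will be assessed by linear regression, with each PD outcome variable as a dependent and each CD outcome variable as an independent variable".
- The interval: "95% confidence intervals (CIs) will be calculated for the identified intercepts and regression coefficients using the Gaussian approach", with the formula printed as "95%-CI of a: a ± 2*Se_a_; 95%-CI of b: b ± 2*SE_b".
- The decision: "If the CIs include 0 and 1 (for intercepts and regression coefficients, respectively), accuracy will be considered adequate".

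The text then moves from patients to facilities: "This same procedure will be applied to test H1b using CD quality indicators and PD quality indicators, which are represented by facility group mean values". Under Study population and recruitment, Study 1, the number of facilities is given: "ten German inpatient rehabilitation facilities (IRFs) were enlisted". No separate multiplier or small-sample correction is stated for H1b.

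Accuracy is one of three validation criteria (with reproducibility and precision), and meeting any two is enough to call a claims-data variable an adequate proxy.

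**The concern.** The article fixes both a confidence level (95%) and a multiplier (2). The two agree when the residual degrees of freedom are large, as at patient level. They do not agree in a straight-line regression through ten facility points, where the residual variance is itself poorly estimated and the t distribution has visibly heavier tails than the normal.

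The interval limits act as a decision rule. If they are too narrow for their label, a truly accurate facility indicator fails each coefficient check more often than the stated level implies, and intervals reported as 95% are mislabelled. Facility indicators are what the planned quality assurance procedure and the facility report cards are to be built on, so the label should be right at that level.

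**Working it through.** **Inputs**

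- Stated level: 95% for each of intercept and slope (Hypothesis 1).
- Multiplier: 2 (Hypothesis 1).
- Model: simple linear regression with two estimated coefficients, so residual df = n − 2.
- H1b: ten facilities (Study population and recruitment), one point each, so df = 8.
- H1a: n = 300 expected for analysis (Sample size, Study 1), so df = 298. If the matched sample is split in half, n = 150 and df = 148.

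**Formula.** With normal residuals, estimate ± 2 SE covers the true coefficient with probability P(|T| < 2), where T follows Student's t on n − 2 df. In the Gaussian limit this is 2Φ(2) − 1.

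**Where the plan's figure reproduces**

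- Gaussian limit: 2Φ(2) − 1 = 95.45%.
- n = 300: 95.36%.
- n = 150: 95.27%.

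The 95% label is therefore about right for H1a.

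**Where it does not: H1b, df = 8.** For even df the probability has a closed form. With t²/df = 4/8 = 0.5, cos²θ = 1/1.5 = 2/3 and sin θ = √(1/3) = 0.57735. Then

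P(|T| < 2) = 0.57735 × [1 + (1/2)(2/3) + (3/8)(4/9) + (15/48)(8/27)]
= 0.57735 × [1 + 0.33333 + 0.16667 + 0.09259]
= 0.57735 × 1.59259 = 0.9195.

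Each interval covers 91.9%, with an error rate of 8.1%. A simulation of 200,000 ten-point regressions (true intercept 0, slope 1, normal errors) gave 92.0% for the intercept and 92.0% for the slope.

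**Multiplier needed.** t(0.975; 8) = 2.306, and 2.306/2 = 1.153, so the correct interval is 15% wider. Simulated coverage with it is 95.0% for both coefficients.

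**If fewer facilities contribute:** 91.4% with nine, 90.8% with eight.

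**What the wider interval does to the decision.** Adequacy is declared when the intervals include 0 and 1, so widening them makes passing easier for every indicator. The table gives an illustration at n = 10. Its settings are assumptions, not figures from the article: claims indicator SD 1, both measures with equal means, and mean/SD of 0, 3 or 10.

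| True state | Passes both checks, ± 2 SE | Passes both checks, ± 2.306 SE |
|---|---|---|
| Accurate (slope 1, r = 0.8) | 86–91% | 91–94% |
| Slope 0.5, residual SD 0.75 | 46–48% | 56–58% |
| No association, equal SDs | 20–22% | 28–30% |

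The gain is about 3 to 5 points for an accurate indicator, against about 8 to 10 points more acceptance of a poor one.

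**The case against.** The strongest reply is that the article openly calls the interval Gaussian and prints the formula. It was written for patient-level outcomes, where it works, and one summarising sentence carried it to H1b. On this view it is a disclosed large-sample approximation, not an arithmetic mistake. That explains how the mismatch arose, but the level is still stated as 95% and the formula does not deliver it on ten points.

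A second reply carries more weight. The narrow interval makes the criterion stricter, so it errs against replacing patient-reported data with claims data. Correcting it loosens the criterion, and more for poor indicators than for good ones. This stands, and it must be named as a cost of the fix. The deeper weakness, that failing to exclude 0 and 1 on ten points counts as accuracy, is left untouched.

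Third, accuracy is one of three criteria of which two suffice, so an indicator that fails it can still be accepted. This stands too and limits the practical effect.

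A reader might go further and infer that the combined rule, which needs both intervals to cover, was also meant to operate at 95%, so that its joint failure rate is another error calling for a joint test of intercept and slope. The article does not support that. It attaches 95% to each interval and never to the pair. Any joint failure rate depends on an assumed correlation and mean-to-SD ratio that the article does not give, and it mixes the effect of requiring two intervals with the effect of the multiplier. A joint test would be a choice of another method, not a correction.

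**Conclusion.** The point holds for H1b only. As written, the facility-level intervals have about 92% coverage per coefficient under a 95% label: an error rate of 8.1% instead of 5%. This assumes one point per facility, all ten facilities contributing and roughly normal residuals; the article describes no pooling over time points or joints. The per-coefficient figure does not depend on how strongly the two indicators are correlated.

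The consequence is modest. Only an intercept or slope lying between 2.0 and 2.31 SE from its target changes status, and only on one of three criteria. It would be too strong to say that H1b verdicts will be wrong; what is wrong is the stated confidence level. H1a is unaffected.

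**What to change.** For H1b, replace the multiplier 2 by the 0.975 quantile of t on n − 2 degrees of freedom, which is 2.306 with ten facilities, and let it follow the number of facilities that actually contribute. Using the t quantile throughout is equally good and leaves H1a practically unchanged. If the sponsor prefers to keep ± 2 SE for H1b, restate its level as about 92%.

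The change is one line of wording and standard software output, with no new data. Its cost is that H1b intervals become 15% wider, so indicators pass the accuracy check more easily whether or not they are accurate. The report should say so, and should not present the correction as a remedy for the low power of a ten-point inclusion rule.

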## Study design and methods

SEQUAR combines two studies in one project: A prospective longitudinal multicenter study collecting patient- and health professional-reported data (study 1), and a retrospective cohort study using health claims data (study 2).

In study 1, patients in orthopedic follow-up rehabilitation after hip or knee arthroplasty and their physicians are repeatedly surveyed with a set of validated instruments at different phases throughout their post-op treatment. The instruments used allow comprehensive assessment of the various (long-term) outcome domains of rehabilitation (PD outcome variables), and are the current best-practice assessment against which the claims data outcomes (CD outcomes) will be tested (see section “Study outcomes”). Facility-level quality indicators based on primary data (PD quality indicators) will be calculated for individual facilities by grouped scale means.

For study 2, health claims data (CD) will be extracted from the AOK health insurance fund database (see section “Sample”). Participants of study 1 are a small subsample of the larger study 2 sample. The large study 2 sample will be used to explore, identify and validate potential CD outcome variables, CD quality indicators, and CD risk factors. The subsample of claims data from study 1 participants will be matched to the outcome variables in the PD dataset resulting from study 1, and split into two subsamples for analysis and validation, respectively. Figure 1 illustrates the data flow.

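### The H1 accuracy rule treats failure to reject intercept 0 and slope 1 as agreement, with no margin, so a pass gets easier as precision falls; this matters most for H1b with ten facilities

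*Protocol article*

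**What the plan says.** Under Data analysis and hypothesis testing (Study 1, Hypothesis 1), the protocol article regresses PD on CD one pair at a time, "with each PD outcome variable as a dependent and each CD outcome variable as an independent variable". Intervals are formed as "95%-CI of a: a ± 2*Se_a_; 95%-CI of b: b ± 2*SE_b". The decision is: "If the CIs include 0 and 1 (for intercepts and regression coefficients, respectively), accuracy will be considered adequate for the outcome variable". No tolerance around 0 or 1, maximum interval width or minimum R² accompanies it.

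Accuracy then feeds the overall decision: "If at least two of the three validation criteria are met, the tested CD outcome variable is considered an adequate proxy". The other two criteria are reproducibility (duplicate SD) and precision (SD of CD no larger than SD of PD). Bland-Altman plots are for graphical evaluation only, with no limit stated.

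For the facility level the article says: "This same procedure will be applied to test H1b using CD quality indicators and PD quality indicators". Study population and recruitment gives the number of units: "ten German inpatient rehabilitation facilities (IRFs) were enlisted in the study". Sample size expects about 300 patients for analysis. Study design and methods says that the matched sample will be "split into two subsamples for analysis and validation, respectively", without proportions. The same section expects a correlation above 0.30 for H1b, but the Hypothesis 1 decision rule does not include that threshold.

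**The concern.** Calling accuracy adequate is a claim of agreement: intercept near 0 and slope near 1. The rule reaches that claim by not rejecting those two values. Absence of evidence against agreement is thus counted as evidence for it. Anything that widens the intervals (few units, weak association, a CD variable with little spread) makes a pass easier, and anything that narrows them makes a pass harder, even for a proxy whose departure is trivial.

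The decision rests on few criteria. A false pass on accuracy needs only one more criterion, and low spread in the CD variable both widens the slope interval and satisfies precision. The result informs whether claims indicators can replace parts of the questionnaire-based procedure.

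**Working it through.** **The plan's own figures.** 600/0.70 = 857 (stated 860); 60/0.70 = 85.7 (stated 86 per facility); 600 × 0.8³ = 307 (stated about 300). These reproduce. No power, precision or margin is stated for the accuracy criterion, so there is no figure of that kind to reproduce.

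**Inputs from the article.** ±2 SE intervals; pass if 0 and 1 are included; n = 10 facilities for H1b; n about 300 for H1a.

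**Assumptions, because the article gives no values.** CD and PD on a common scale; SD(PD) = 1; both means 1.5 SD above zero; independent units; true slope β; k = SD(CD)/SD(PD). An equal split of the patient sample (n = 150) is also an assumption. Precision is taken as SD(CD) ≤ SD(PD).

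**Approximate arithmetic for the slope.** r = βk and SE(b) ≈ √(1 − r²) / (k√n). A slope of 1 tends to be included when 2·SE(b) is not small against |1 − β|.

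- n = 10, β = 0, k = 0.25: SE = 1/(0.25 × 3.162) = 1.26. Half-width 2.53 against a gap of 1, so it usually passes.
- n = 10, β = 0.5, k = 1: SE = 0.866/3.162 = 0.274. Half-width 0.55 against a gap of 0.5, so it passes about half the time.
- n = 300, β = 0.5, k = 1: SE = 0.866/17.32 = 0.050. Half-width 0.10 against 0.5, so it is rejected.
- n = 300, β = 0.5, k = 0.25 (r = 0.125): SE = 0.992/(0.25 × 17.32) = 0.229. Half-width 0.46 against 0.5, so it passes a little under half the time.
- n = 300, β = r = 0.95, k = 1: SE = 0.312/17.32 = 0.018. Half-width 0.036 against a gap of 0.05, so it usually fails.

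**Simulation of the full rule (intercept and slope together).** Two runs differ by about one percentage point at most.

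H1b, n = 10:

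| True slope | Condition | k = 1 | k = 0.5 | k = 0.25 |
|---|---|---|---|---|
| 0 | accuracy | 20% | 63% | 83–84% |
| 0 | accuracy + precision | 18–19% | 63% | 83–84% |
| 0 | accuracy + sample r > 0.30 | 10–11% | 19% | 19–20% |
| 0.5 | accuracy | 53% | 82% | 89% |
| 0.5 | accuracy + precision | 42% | 82% | 89% |
| 0.5 | accuracy + sample r > 0.30 | 47% | 44% | 29% |

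H1a, true slope 0.5, accuracy:

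| n | k = 1 | k = 0.5 | k = 0.25 |
|---|---|---|---|
| 150 (if halved) | 0% | 11–12% | 65% |
| 300 | 0% | 0.7% | 41% |
| 600 | 0% | 0% | 13% |

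Very good proxy (r = slope = 0.95, k = 1):

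| n | Accuracy as written | Slope interval inside 0.80–1.25 (illustrative) |
|---|---|---|
| 10 | 85% | 19% |
| 150 | 47% | 100% |
| 300 | 20% | 100% |
| 600 | 2% | 100% |

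The rule as written passes this proxy less often as data accumulate; the margin rule passes it more often. The second column tests only the slope part of a margin rule.

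**Interval label.** With n = 10 there are 8 degrees of freedom. P(|t₈| < 2) = 0.919, so ±2 SE covers about 92%, and the 95% quantile is 2.31.

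**The case against.** Several points on the other side are sound.

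- **The H1b correlation.** The article does state an expected correlation above 0.30. Requiring it alongside accuracy would cut the H1b pass rates to about 10–20% (slope 0) and 30–47% (slope 0.5). The decision rule does not contain it, however, so the rates without it describe the plan as written.
- **Patient level.** A reader might infer that the rule passes poor proxies generally. The figures do not support that: at n = 300 a slope of 0.5 passes 0% at equal SDs and 0.7% at SD ratio 0.5. The patient-level problem is confined to CD variables with much smaller spread. The n = 150 figure rests on an assumed split, since halves are specified only under Hypothesis 2.
- **Good proxies.** A reader might infer that near-perfect proxies will be refused overall. That holds for the accuracy criterion only. If duplicate SD is read as a percentage of the mean and 20% or less counts as adequate, the r = 0.95 proxy meets reproducibility almost always at n ≥ 150, and its two-of-three pass rate stays near 50% at n = 150, 300 and 600. The remaining failures at large n come from comparing two equal SDs.
- **Interval label.** A reader might infer that ±2 SE inflates passes. It does the reverse: with 2.31 in place of 2, the slope-0.5, equal-SD case at n = 10 passes 63% instead of 53%. It is a labelling error, not a cause of the false passes.
- **Scale.** The candidate CD variables are prescriptions, aids and care levels. On raw, different scales most pairs would fail intercept 0 and slope 1. That is a separate difficulty with the same criterion and does not make a rule without a margin valid.

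**Conclusion.** The point holds in bounded form. The article writes out a complete decision rule, so this is not a detail left to an unseen analysis plan, and the rule rewards imprecision. For H1b with ten facilities the effect is large: an unrelated indicator passes accuracy 20–84% of the time and can be declared an adequate proxy on accuracy plus precision 19–83% of the time. The lower end applies at equal SDs, so the documents do not support saying that every H1b scenario is badly affected. For H1a the false-pass risk is limited to CD variables with far smaller spread than the PD variable. The opposite error, failing a very good proxy on accuracy, appears already at n = 300 (20% pass) but is partly offset in the final decision.

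All rates depend on the assumed common scale, means, spreads, slopes and independence of units. The direction of the defect does not.

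**What to change.** Replace inclusion of 0 and 1 by an equivalence rule. Accuracy is adequate only if the whole interval for the slope and the whole interval for the mean CD–PD difference, on a common or calibrated scale, lie inside margins that the sponsor fixes before linkage. Any other result is reported as inconclusive, not as adequate. A slope margin of 0.80–1.25 and a difference margin of ±0.5 SD are illustrations only.

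Reconcile the margins with the expected correlation above 0.30 for H1b: at equal SDs slope equals r, so a lower slope margin of 0.80 asks for far more than 0.30. State whether that correlation is part of the decision.

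For H1b use t quantiles with n − 2 degrees of freedom (2.31 at n = 10), together with the margin rule and not on their own. State in advance that ten facilities will mostly give an inconclusive agreement result.

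The cost is wording and the choice of margins; no new data are needed. The downside is that fewer pairs will be declared adequate, and the way H1b is judged changes in substance.
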